**Results:**

The implementation strategy, designed with input from the consultation and observational studies, is expected to lead to an increased number of unique visits to the TEN website in the 3 months following the introduction of the implementation strategy. The observational study is expected to observe high service acceptability. Moderate improvements to general mental health (DQ-5, WSAS) and a reduction in workplace- and treatment-related mental health stigma (EASI) between the baseline and 1-month time points are expected.

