#### Recruitment

Participants for the observational study will be recruited through advertisements on social media, emails sent to health professionals on an internal Black Dog Institute mailing list, emails from TEN partner organizations, and information about the study on the Black Dog Institute and TEN websites. Prospective participants who engage with advertisements or study details on the TEN website will be redirected to the online participant information statement and consent form. Participants who elect not to participate in the study will be provided with a link to TEN and informed they may use the service freely and anonymously.

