**Figure 3 figure3:**
[figure not shown]
Flowchart depicting a progression through the observational study. DQ-5: Distress Questionnaire; EASI: Endorsed and Anticipated Stigma Inventory; GAD-7: Generalized Anxiety Disorder; OBI-16: Oldenburg Burnout Inventory; PCL-5: Posttraumatic Stress Disorder Checklist; PHQ-9: Patient Health Questionnaire; SAS CI 360: SAS Customer Intelligence 360; TEN: The Essential Network; WSAS: Work and Social Adjustment Scale.

After consenting, participants will provide information on demographics and mental health (Table 2), service acceptability (Table 3), and complete baseline mental health and stigma outcomes (Table 4). Mental health outcomes are identical to the TEN online assessment. To avoid the participants needing to repeat the online assessment on the TEN website after completing the baseline mental health outcomes, the survey baseline will provide the same assessment feedback. Participants will then be provided with a link to the TEN website and asked to engage with the service naturalistically for 6 months. The link provided to each participant is unique and associated with their consent record number. User engagement (eg, pages viewed) with the TEN website is recorded automatically through the SAS Customer Intelligence 360 (SAS CI 360) platform. SAS CI 360 is a commercial website analytics package that records website use. Using unique TEN website links sent to participants, their TEN website use will be extracted and linked to their other study data. Participants will be recommended to bookmark this link, and their unique link will be provided to them by email at baseline and after the 1-month follow-up.

**Table 2 table2:** Questions examining demographic and baseline mental health.

Baseline question	Time point	Classification	Type of question
Gender	Baseline	Demographics	Single selection
Age	Baseline	Demographics	Single selection
Where are you located?	Baseline	Demographics	Single selection
What best describes your profession?	Baseline	Demographics	Single selection
Have you previously used the TEN^a^ service?	Baseline	Mental health	Yes/no
COVID-19 has affected your mental health.	Baseline	Mental health	Likert scale
Have you ever seen a doctor, counsellor, or other health professional about your mental health?	Baseline	Mental health	Yes/no
If you were seeking help for a mental health problem, what type of service would you most likely choose?	Baseline	Mental health	Multiple selection

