#### Participants

Participants in the implementation study will be self-identified Australian HCWs.

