#### Data Collection

Quantitative data will be collected through an audit of usage of the TEN website and TEN Clinic for a period of 3 months both before and after the implementation of the implementation strategy. Although the exact implementation strategy will be determined by the results of the consultation study, example strategies from the literature include identifying “champions” within an organization to drive uptake or develop incentives, such as continuing professional development activities [32]. TEN website data include completed online assessments automatically recorded on UNSW servers and website analytics (eg, number of unique users, pages viewed) automatically collected through the SAS CI 360 platform. TEN Clinic data include service analytics data, which are routinely captured by clinicians in the delivery of TEN Clinic services. Surface-level nonidentifiable TEN Clinic data will be examined as part of the implementation study (eg, number of referrals, number of consultations).

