### Study 3: Implementation Study

#### Data Analysis

Descriptive statistics will be used to report usage of the TEN website and TEN Clinic over the 3-month period both pre- and postimplementation strategy. The *t* test will be used to compare overall usage of the TEN service for these 2 periods. Linear mixed models will examine latent growth in service usage following the implementation strategy.

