## Discussion

### Summary

Blended digital and person-to-person care has significant potential to support mental health of HCWs through service flexibility and widespread availability. To date, however, the potential of blended care has been hampered by a lack of knowledge around the optimal implementation of such services. The CFIR framework provides a structured approach to implementation that will guide the development and application of implementation strategies for TEN. Using a implementation-effectiveness hybrid study, this implementation study will span 3 separate components. Through a series of consultations, an implementation strategy tailored to HCWs will be developed. Feedback on this strategy will be provided by HCWs participating in an observational study of TEN, from which data on the effectiveness of TEN will be acquired. Finally, the implementation strategy will be implemented and compared against the previous engagement strategies. The knowledge created by this project will inform the development and delivery of blended mental health services for HCWs, including how such services can be rapidly launched and implemented during times of crisis.

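### Study 3's before/after count of TEN usage includes visits that Study 2 itself generates, so a true rise in uptake is diluted or understated by an amount that depends on undated windows

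*Protocol article*

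**What the plan says.** **Study 3.** The Data Collection section describes "an audit of usage of the TEN website and TEN Clinic for a period of 3 months both before and after the implementation" of the strategy. The website data include "website analytics (eg, number of unique users, pages viewed) automatically collected through the SAS CI 360 platform". On the population, the article says only "Participants in the implementation study will be self-identified Australian HCWs". Under Data Analysis, a *t* "test will be used to compare overall usage of the TEN service for these 2 periods". The Abstract expects an "increased number of unique visits to the TEN website in the 3 months following the introduction of the implementation strategy".

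**Study 2.** Recruitment runs through social media, a mailing list, partner organizations' emails, and the Black Dog Institute and TEN websites. On decliners, the Recruitment section says "Participants who elect not to participate in the study will be provided with a link to TEN". On those who consent, the Data Collection section says "Participants will then be provided with a link to the TEN website and asked to engage with the service naturalistically for 6 months". Each participant's link is unique and is emailed at baseline and again after the 1-month survey. The TEN Service Engagement section confirms that SAS CI 360 logs every interaction with the site.

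**Order.** The Discussion summary states "Feedback on this strategy will be provided by HCWs participating in an observational study of TEN", and places the launch of the strategy after that. The Abstract also says the observational study feeds into the strategy's design.

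**The concern.** Uptake is the primary objective, and the before/after contrast is the only test of it. The before window is meant to show usage under the previous engagement strategies. Study 2 is itself a source of TEN visits: it recruits health care workers, hands them a link and asks them to use the site for 6 months. It starts before launch, and its visits land in the same platform counts that Study 3 compares.

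If those visits fall mostly in the before window, that window is raised and the strategy looks less effective than it is. If they fall equally in both windows, they add the same constant to each and shrink the relative change. No test on the totals can separate the two sources afterwards. Potential Limitations names pandemic events as a threat to uptake and notes that the unique links are error prone, but it does not name Study 2 as a source of Study 3 traffic.

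The overlap also runs the other way. Participants who are between months 2 and 6 when the strategy launches may be exposed to it. The Kaplan-Meier persistence curve would then mix use of TEN alone with use of TEN under the strategy.

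**Working it through.** **Study 2 users, S.** The Sample Size section gives at least 105. This reproduces with a reduction of 3.87, SD 8.9, two-sided α = .05, 80% power and time points treated as uncorrelated: 2 × [8.9 × (1.960 + 0.842)/3.87]² ≈ 83.0, rounded up to 84, and 84/0.8 = 105. So S = 105 is the planned minimum number of people directed to TEN, before any decliners.

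**Organic users per 3-month window, U.** The article gives no visitor count. Its only volume figure is 249 assessments between June 28 and August 28, 2021, about 2 months: 249/2 × 3 = 373.5 per 3 months. If 10%, 25% or 50% of unique users complete an assessment (assumption), U = 373.5/0.10 = 3,735, 373.5/0.25 = 1,494, or 373.5/0.50 = 747.

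**Observed change.** Let g be the true relative rise and r the share of Study 2 users, all active before launch, who are also active in the after window:

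observed change = [U(1 + g) + rS]/(U + S) − 1

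With g = 20% and S = 105:

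| U | r = 1 (both windows) | r = 0.25 (assumed) | r = 0 (before window only) |
|---|---|---|---|
| 3,735 | 4,587/3,840 − 1 = +19.5% | 4,508.25/3,840 − 1 = +17.4% | 4,482/3,840 − 1 = +16.7% |
| 1,494 | 1,897.8/1,599 − 1 = +18.7% | 1,819.05/1,599 − 1 = +13.8% | 1,792.8/1,599 − 1 = +12.1% |
| 747 | 1,001.4/852 − 1 = +17.5% | 922.65/852 − 1 = +8.3% | 896.4/852 − 1 = +5.2% |

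**When the sign changes.** The observed change is negative when g < (1 − r)S/U. At r = 1 this cannot happen for a positive g. At r = 0 with S = 105 the thresholds are 105/3,735 = 2.8%, 105/1,494 = 7.0% and 105/747 = 14.1%. A true 20% rise therefore keeps its sign throughout the table. At the extreme where every unique user completes an assessment (U = 373.5), the threshold is 105/373.5 = 28.1%, and a true 20% appears as 448.2/478.5 − 1 = −6.3%.

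**Can the overlap be avoided by timing?** Participants use TEN for 6 months and the before window lasts 3. The last participant's follow-up ends before that window opens only if launch comes at least 6 + 3 = 9 months after the last enrolment. The article states no such gap.

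**Which measures are affected.** Unique users and page views are exposed. The size for page views cannot be computed, because pages per user are not given. Completed online assessments are less exposed: Study 2 takes its baseline assessment in its own survey so that participants need not repeat it on TEN.

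**The case against.** The strongest reply is that this rests on silence and on timing the text does not give. The windows are undated, ethics approval for Study 3 is sought only after the strategy is designed, and Figure 2 is not shown. A filter on analytics counts could sit in the full protocol or analysis plan. That stands as a limit on direction and size. It does not remove the point: the article fixes an all-user count, the order of the studies and the contrast, and on those terms Study 2 visits are counted.

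A reader might infer that the bias runs one way and could turn a real gain into an apparent loss. The documents do not support that as a general claim. Participants are asked to use TEN for 6 months and receive their link again after month 1, so many may appear in both windows, which dilutes without reversing. Recruitment continuing after launch would push the estimate upward. A reversal of a 20% effect at the assumed volumes needs stacked assumptions. With three decliners per participant all following their link, S = 105 × 4 = 420. If all of these are new users, none returns after launch and U = 747, then 896.4/1,167 − 1 = −23.2%. With the same 420 in both windows the result is (896.4 + 420)/1,167 − 1 = +12.8%. The article gives no number of decliners. Some Study 2 users would have visited anyway, since recruitment uses the TEN website and the baseline survey asks about previous use. People who respond to advertisements are sent to the consent form, not straight to TEN.

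A reader might also infer that all the study traffic can be identified and removed. It cannot. Decliners are promised anonymous use, the Clinic data for Study 3 are nonidentifiable, and participants may reach the site without their link.

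**Conclusion.** The point holds in a limited form. As described, the primary contrast includes traffic made by the sponsor's own observational study. For a true 20% rise in unique users, the 105 planned participants reduce the observed figure to between +17.5% and +19.5% if they are active in both windows, and to between +5% and +17% if they are active only before launch. These ranges rest on assumed volumes of 747 to 3,735 users per window and on counting all participants as additional users. Reversal of sign is possible only with low traffic, many decliners or a small effect, and the documents do not show that any of these applies. Completed assessments are less affected. The mixing of pre- and post-launch use in the persistence curve is a secondary consequence, which arises only if launch falls inside participants' 6-month follow-up.

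**What to change.** 1. State the dates of both 3-month windows relative to the opening and closing of Study 2 recruitment.
2. In Study 3, exclude sessions opened through Study 2 unique links from the website counts in both windows, and report the contrast with and without them.
3. Record the launch date. Keep the planned 6-month persistence curve for Study 2 and add a sensitivity analysis censored at launch.
4. Add to the limitations that visits by decliners and by participants who bypass their link remain in the counts.

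The cost is small: a filter on links that Study 2 already issues, one recorded date and one extra analysis. The website counts become slightly smaller. The correction is partial, because the traffic in item 4 cannot be separated and the filter does not reach the Clinic data. Tagging decliners' links is not proposed, because it sits badly with the anonymous use they are promised.

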## Results

### Study 1: Consultation Study

#### Data Analysis

A framework analysis using the CFIR will be conducted to thematically analyze and interpret the semistructured interviews from the consultations. Each transcript will be analyzed separately by 2 investigators who will meet periodically throughout data collection to discuss emerging themes and resolve discrepancies. The sample size is expected to be sufficient for thematic saturation [33].

### Study 2: Observational Study

#### Data Analysis

Descriptive statistics will be used to report the overall acceptability of TEN. The results from the observational study will be analyzed using linear mixed models to examine changes in reported psychosocial benefits over time (ie, baseline, 1 month). Patterns of service engagement and baseline outcome severity will be classified using cluster analyses or latent class analyses. These patterns will be used to examine how service engagement influences outcomes, as well as stratify participants baseline outcomes for subset analysis. Kaplan-Meier curves with TEN engagement data will be used to examine persistence with TEN over the course of the 6-month follow-up (ie, when participants ceased accessing the service). Missing data will be addressed using maximum likelihood estimation. This will answer the research questions by examining the acceptability of TEN among HCWs, patterns of service usage over time, any benefits observed after engaging with the TEN service, and persistence with the service over time.

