**Methods:**

The implementation study contains 3 components: (1) a consultation study with up to 39 stakeholders or researchers with implementation experience to design an implementation strategy, (1) a longitudinal observational study of at least 105 HCWs to examine the acceptability of TEN and the effectiveness of TEN at 1 and 6 months in improving mental health (as assessed by the Distress Questionnaire [DQ-5], Patient Health Questionnaire [PHQ-9], Generalized Anxiety Disorder [GAD-7], Oldenburg Burnout Inventory [OBI-16], and Work and Social Adjustment Scale [WSAS]) and reducing mental health stigma (the Endorsed and Anticipated Stigma Inventory [EASI]), and (3) an implementation study where TEN service uptake analytics will be examined for 3 months before and after the introduction of the implementation strategy.

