After using TEN for 1 month, participants will be provided with a survey containing service acceptability (Table 3), mental health and stigma outcomes (Table 4), feedback on the implementation strategy (Table 5), and self-reported service engagement (Table 5). After completing the survey, participants will be informed that their TEN website usage will be monitored for a further 5 months to examine persistence with the service. After 6 months, participants will be provided with a follow-up survey about employment (Table 2) and mental health outcomes (Table 4).

**Table 5 table5:** Questions examining the implementation strategy and service engagement.

Question		Type of question

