#### Mental Health and Psychosocial Outcomes

Mental health and psychosocial outcomes will be examined through surveys provided to participants at the 0-, 1-, and 6-month time points. The questionnaires used will examine a range of outcomes, including the Distress Questionnaire (DQ-5) [25], the Patient Health Questionnaire (PHQ-9) [26], Generalized Anxiety Disorder (GAD-7) [27], the Posttraumatic Stress Disorder Checklist (PCL-5) [28], the Oldenburg Burnout Inventory (OBI-16) [29], the Work and Social Adjustment Scale (WSAS) [30], and the Endorsed and Anticipated Stigma Inventory (EASI) [31] (Table 4). To address workplace stigma unique to HCWs, a question addressing mandatory reporting concerns was added to the workplace stigma subscale of the EASI. Except for the EASI, these questionnaires are identical to those used in the TEN online assessments. Completed online assessments are automatically collected and stored on University of New South Wales (UNSW) servers. Any completed online assessments will be linked back to the participants using their internet protocol (IP) address collected during online consent.

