#### Sample Size

Sample size calculations were based on the primary analysis: a random intercepts mixed effects model estimating change in WSAS scores from baseline to 1 month in a single group of participants. Estimated scores at baseline were derived from 249 TEN mental health assessments performed between June 28 and August 28, 2021. These scores represent HCWs self-selecting to engage with the TEN service and, as such, are analogous to the observational study participants at baseline. The mean of scores in this group was 14.9 (SD 8.9). The cut-off score for a clinical case on the WSAS is 11; thus, to reduce from the mean untreated score of 14.9 to a subclinical score requires a 3.87-point reduction. With variance-covariance of random effects derived from the SD in WSAS scores from current TEN users of 8.9, and accounting for 20% attrition, a sample size of at least 105 is required to detect a true reduction of this size with 80% power and a significance level of α=.05.

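### The Study 2 outcome model covers only baseline and 1 month, so the stated aim of effectiveness at 6 months has no analysis that estimates change

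*Protocol article*

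**What the plan says.** All references are to the protocol article.

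- **Aim.** Abstract, Methods: the observational study is to examine "the effectiveness of TEN at 1 and 6 months in improving mental health". The same sentence adds stigma, measured by the EASI.
- **Schedule.** Study 2, Mental Health and Psychosocial Outcomes, where the timing is fixed for these measures: they "will be examined through surveys provided to participants at the 0-, 1-, and 6-month time points". Among the instruments listed next is the EASI.
- **6-month survey.** Study 2, Data Collection: "After 6 months, participants will be provided with a follow-up survey about employment (Table 2) and mental health outcomes (Table 4"). Table 4 lists seven instruments, the EASI among them. The description of the 1-month survey in the same paragraph names stigma separately; the 6-month description does not.
- **Primary analysis.** Study 2, Sample Size: "a random intercepts mixed effects model estimating change in WSAS scores from baseline to 1 month in a single group of participants".
- **Outcome model.** Results, Study 2, Data Analysis: "linear mixed models to examine changes in reported psychosocial benefits over time (ie, baseline, 1 month").
- **The one analysis that names 6 months.** Same section: "Kaplan-Meier curves with TEN engagement data will be used to examine persistence with TEN over the course of the 6-month follow-up".

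The Data Analysis section also plans to relate patterns of engagement to outcomes, without giving a time point, and to handle missing data by maximum likelihood. It closes by saying that the analyses will answer the research questions.

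**The concern.** The article does not leave the time points of the outcome model open. It states them, and the abbreviation *ie* makes the list exhaustive. The list leaves out a visit at which the abstract promises an effectiveness result and at which participants are asked to complete the outcome battery.

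Followed literally, the study could report a change at 1 month but could not say whether it lasts. If 6-month results were reported anyway, the model behind them would not have been fixed in this document and could be chosen after the data are seen. That matters in a single-group pre/post study, because the limitations section itself accepts that these outcomes can improve without intervention.

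**Working it through.** **1. Matching aim, data and analysis at each time point**

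| | 1 month | 6 months |
|---|---|---|
| Effectiveness aim (Abstract) | yes | yes |
| Outcomes scheduled (Data Collection; Outcomes section) | yes | yes |
| Sample size (Sample Size) | yes, WSAS | no |
| Expected results (Abstract) | yes | no |
| Outcome mixed model (Data Analysis) | yes | no |
| Kaplan-Meier (Data Analysis) | not applicable | website engagement only |
| Engagement patterns against outcomes (Data Analysis) | no time point given | no time point given |

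The Kaplan-Meier curve describes when people stop visiting the site, which says nothing about change in distress, impairment or stigma. The engagement-pattern analysis might use 6-month scores, but it relates usage to outcome and does not estimate change from baseline. The 6-month column therefore has an aim and data but no estimate of change.

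**2. Does the plan's sample size depend on this?**

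Inputs from Sample Size: reduction 3.87, SD 8.9, power 80%, α = 0.05 (two-sided assumed), attrition 20%. With variance of change 2·SD²·(1 − ρ) and ρ = 0:

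n = 2 × 8.9² × (1.96 + 0.8416)² / 3.87² = 83.0, rounded up to 84; 84 / 0.80 = 105.

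The stated 105 is reproduced. It rests on the 1-month contrast alone, so adding a 6-month contrast does not change it.

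**3. Does leaving out month 6 weaken the 1-month estimate?**

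With 105 people at baseline and 84 at 1 month (105 × 0.80), the maximum likelihood variance of the two-visit change under equal variances and correlation ρ is

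SD² × [(1 − ρ²)/84 + (1 − ρ)²/105].

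For ρ = 0.5: 79.21 × (0.75/84 + 0.25/105) = 0.896, SE 0.946. For ρ = 0.3 the SE is 1.108, and for ρ = 0.7 it is 0.741.

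The calculation was repeated with a third visit under the same correlation. Neither ρ nor 6-month response is in the documents, so these are assumptions: 60% to 80% of 1-month responders and 20% to 50% of 1-month non-responders seen at 6 months.

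| ρ | SE, two visits | SE, three visits | variance reduction |
|---|---|---|---|
| 0.3 | 1.108 | 1.106 to 1.107 | 0.2% to 0.4% |
| 0.5 | 0.946 | 0.942 to 0.945 | 0.4% to 1.0% |
| 0.7 | 0.741 | 0.735 to 0.738 | 0.7% to 1.6% |

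The gain in precision for the 1-month contrast is negligible.

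**4. Would a 6-month contrast be worth having?**

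Power for a 3.87-point WSAS change at 6 months is Φ(3.87 / √(2·SD²·(1 − ρ)/m) − 1.96), with m = 105 × (1 − attrition). Attrition at 6 months and ρ are assumed.

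| 6-month attrition | m | ρ = 0 | ρ = 0.3 | ρ = 0.5 |
|---|---|---|---|---|
| 20% | 84 | 80% | 92% | 98% |
| 40% | 63 | 69% | 83% | 93% |
| 60% | 42 | 51% | 66% | 80% |

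With moderate correlation, the planned sample gives useful power at 6 months even with twice the attrition that the plan allows for.

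**The case against.** The best defence is that the restriction is deliberate. Sample Size defines the primary analysis as baseline to 1 month, the expected results in the abstract use the same window, and the study objectives give no time point for mental health change. Detail on a secondary time point is often left to a fuller protocol or a statistical analysis plan, and neither is shown. This stands for the primary contrast, which is internally consistent. It does not cover the 6-month aim. The Data Analysis sentence describes the results of the observational study in general, and its list of visits is closed. An analysis plan that added month 6 would contradict it, and one that followed it would leave the abstract's aim unanswered.

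Readers might be tempted by three stronger inferences, and the documents do not support them.

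- *That the 1-month primary estimate is compromised because people who miss month 1 are lost.* Planned attrition is 105 × 0.20 = 21 people, but maximum likelihood still uses their baseline scores; only any month-6 scores go unused. A bias argument would need 1-month dropout to be related to later scores and those people to return at 6 months. The documents give no figures on either.
- *That stigma is not measured at 6 months.* The Outcomes section lists the EASI at all three time points, and the 6-month survey refers to Table 4, which contains it. The shorter label is loose wording.
- *That month-6 data play no part in any analysis.* The engagement-pattern analysis could use them, although not to estimate change from baseline.

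**Conclusion.** The point holds as a conflict within the article: a stated effectiveness aim at 6 months, outcomes scheduled at 6 months, and an outcome model whose closed list of visits ends at 1 month. What is lost is the estimate of change from baseline to 6 months. This conclusion rests on the text alone and needs no numerical assumption.

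The primary 1-month WSAS contrast and N = 105 are essentially unaffected. The 0.2% to 1.6% figure assumes a compound-symmetric covariance, SD 8.9 at every visit, ρ between 0.3 and 0.7 and the response rates given above. It addresses precision only and does not settle whether dropout is informative.

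**What to change.** Amend the Study 2 Data Analysis section so that the linear mixed model includes baseline, 1 month and 6 months with time as a categorical factor. Keep the 1-month WSAS contrast from Sample Size as primary and name the 6-month contrast as secondary. The random-intercepts structure already stated there can stay; this point does not require a different covariance. The alternative is to withdraw the 6-month effectiveness aim from the abstract.

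In the same edit, align the description of the 6-month survey in Data Collection with the Outcomes section, so that both state that the EASI is included.

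The cost is a change of wording and a small amount of extra analysis. The 6-month survey is already planned, and N does not change.

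### The Study 2 outcome model names only baseline and 1 month, so the 6-month effectiveness aim has no stated analysis

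*Protocol article*

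**What the plan says.** **Aim.** The Abstract (Methods) of the protocol article says the observational study will examine "the effectiveness of TEN at 1 and 6 months in improving mental health".

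**Data collected.** The Study 2 section on mental health and psychosocial outcomes has the instruments completed in "surveys provided to participants at the 0-, 1-, and 6-month time points". Study 2, Data Collection agrees: "After 6 months, participants will be provided with a follow-up survey about employment (Table 2) and mental health outcomes (Table 4".

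**Analysis.** Under Results, Study 2, Data Analysis, outcome change is to be studied with "linear mixed models to examine changes in reported psychosocial benefits over time (ie, baseline, 1 month". The same paragraph adds: "Kaplan-Meier curves with TEN engagement data will be used to examine persistence with TEN over the course of the 6-month follow-up". It also plans to group participants by engagement and baseline severity and relate engagement to outcomes, without giving a time point.

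**Sizing.** Study 2, Sample Size names as the primary analysis "a random intercepts mixed effects model estimating change in WSAS scores from baseline to 1 month in a single group of participants". The Abstract (Results) likewise states expected improvements for baseline to 1 month only.

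**The concern.** The aim and the survey schedule include 6 months; the model that would estimate change does not. The article introduces the model's time points with an abbreviation meaning *that is*, not *for example*, so the list reads as complete.

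What is at stake is whether any improvement lasts. The Potential Limitations section says there is no control arm and that common mental health outcomes can improve without intervention. Persistence or loss of change at 6 months is then one of the few further pieces of evidence the design can offer, though it would not replace a control group. Followed literally, the analysis would produce no such estimate, and the effectiveness aim in the Abstract would be only half met.

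A smaller consequence concerns missing data, which the section handles by maximum likelihood. In a two-wave model, a participant who misses month 1 but answers at month 6 contributes only a baseline score.

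**Working it through.** The point rests on the text, so the places are set side by side first.

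| Place in the protocol article | Time points for outcomes |
|---|---|
| Abstract, Methods (aim) | 1 and 6 months |
| Study 2, Mental Health and Psychosocial Outcomes | 0, 1, 6 months |
| Study 2, Data Collection | Table 4 outcomes in the 6-month survey |
| Abstract, Results (expected change) | baseline to 1 month |
| Study 2, Sample Size (primary analysis) | baseline to 1 month |
| Study 2, Data Analysis, mixed models | baseline, 1 month |
| Study 2, Data Analysis, Kaplan-Meier | 6 months, but the event is ceasing to use the service |
| Study 2, Data Analysis, engagement classes | none given |

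The Kaplan-Meier analysis uses no symptom score. The engagement-class analysis neither includes nor excludes 6-month scores, and relating engagement to outcomes would not by itself give an overall change. So no listed analysis supplies the 6-month estimate.

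**The plan's own figure.** Inputs from Sample Size: WSAS reduction 3.87, SD 8.9, power 80%, α = 0.05 (taken as two-sided), attrition 20%. With within-person correlation r, the SD of change is 8.9 × √(2(1 − r)). At r = 0 this is 8.9 × √2 = 12.59.

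- n = (12.59 × (1.960 + 0.842) / 3.87)² = 83.02, rounded up to 84.
- 84 / (1 − 0.20) = 105.

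The stated 105 is reproduced. It belongs to the baseline-to-1-month contrast; 6 months plays no part in it.

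**What 6 months might offer.** The document gives no correlation between waves and does not tie the 20% attrition to a time point. The following is therefore an illustration. It assumes 105 recruited, a true 3.87-point change at 6 months and SD 8.9 at both waves. With k = 105 × (1 − attrition), power = Φ(3.87 × √k / (8.9 × √(2(1 − r))) − 1.96).

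| Total attrition by 6 months (assumed) | k | r = 0 | r = 0.3 | r = 0.5 | r = 0.7 |
|---|---|---|---|---|---|
| 20% | 84 | 80.5% | 92.0% | 97.9% | 99.9% |
| 40% | 63 | 68.5% | 83.1% | 93.2% | 99.4% |
| 60% | 42 | 51.3% | 66.3% | 80.5% | 95.3% |

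Across these assumptions power runs from about 51% to almost 100%, so the document supports neither adequacy nor inadequacy at 6 months.

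**The case against.** The best defence is that the article consistently makes 1 month the main time point: it is the primary analysis, the basis for the sample size and the period for which improvement is expected. Mental health change is also a secondary objective; the primary one is the implementation strategy. The omission biases no planned estimate and loses no data. All of that stands, and it limits the severity.

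A second defence is that this is a condensed article, and secondary contrasts are often left to a fuller plan. That stands only in part. Had the article been silent on time points, there would be nothing to raise. It states them, and they conflict with its own aim and schedule. A fuller plan could add 6 months, but the text here would still need correcting.

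Three stronger readings are tempting but not supported:

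- **That 6-month change will never be estimated, or only after the data are seen.** A plan not shown may cover it. The supportable statement is that no analysis given here does so.
- **That the random-intercept model is wrong because it forces equal correlations between unequally spaced waves.** The article proposes that model for two waves, where there is only one correlation. It nowhere extends it to three.
- **That 1 month is too short for the consultations TEN offers.** The article gives a maximum of 5 sessions but no period for completing them.

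**Conclusion.** The inconsistency is real and moderate. The article promises effectiveness at 6 months and schedules the instruments then, but lists the outcome model's time points without that wave and offers no other analysis that estimates overall 6-month change. This conclusion rests on reading the parenthesis as a complete list, which is its plain meaning.

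The primary WSAS contrast from baseline to 1 month, and the 105 participants derived for it, are untouched. No number can be put on the loss beyond saying that one of three scheduled outcome waves has no stated outcome analysis. A reader might infer that a 3.87-point change would be detectable at 6 months without more participants. That depends on the assumed correlation and later attrition, and fails for several combinations in the table above.

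**What to change.** In Study 2, Data Analysis, specify a linear mixed model with time as a three-level factor (0, 1 and 6 months), preferably with an unstructured within-person covariance. Keep baseline to 1 month on the WSAS as the primary contrast, and name baseline to 6 months as a secondary contrast for each instrument collected at 6 months. State whether the engagement-class analysis uses 1-month scores, 6-month scores or both.

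If 6-month outcomes are not to be analysed for effectiveness, remove 6 months from that claim in the Abstract instead.

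The cost is small. No new data or participants are needed. An unstructured covariance for three waves has 3 variances and 3 covariances, six parameters, against two for a random-intercept model (intercept and residual variance). In return, people who miss month 1 but answer at month 6 contribute more than a baseline score. The 6-month estimate should be reported with its confidence interval and the number responding, since its precision depends on attrition and correlation that the document does not give.
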